### Secondary outcomes

Secondary outcomes include BP control, implementation fidelity, and TASSH sustainability. BP control is defined as a BP less than 140/90 mm Hg. For those consented and enrolled, at baseline visit, three BP readings will be taken by nurses using an automated BP monitor with the participant seated comfortably for 5 min prior to the measurements, following standard guidelines. The average of the latter two BP readings will be used as the measure for each visit. The same procedure will be followed for each participant visit, including the 12-month visit. Uncontrolled BP is defined by an average clinic systolic *BP* ≥ 140 mm Hg or diastolic *BP* ≥ 90 mm Hg following the guidelines set forth by WHO for CVD treatment [31, 32] and in accordance with the Nigeria Hypertension Treatment Protocol.

Fidelity to TASSH will be measured throughout the study and defined by five dimensions: (1) adherence to the program protocol, (2) dose of the program delivered, (3) quality of program delivery, (4) participant responsiveness, and (5) program differentiation. Tools to assess fidelity were developed for this study and adapted from the current literature [39–41]. Fidelity measures will evaluate adherence from the perspective of the PF, nurses, and the participants.

Sustainability is defined as the maintenance of TASSH adoption at HIV clinics at 18 months (6 months after the end of each cohort’s TASSH + PF phase). Sustainability will be assessed similarly to adoption (as defined above) and qualitatively, based on interviews with nurses and clinic leadership at 18 months. The research coordinator will conduct the interviews with two nurses and one key leadership personnel at each clinic. The interviews will be guided by i-PARiHS and inquire about attitudes regarding TASSH implementation, barriers, facilitators, and implications for scalability. All interviews will be recorded, transcribed, and analyzed with NVivo Version 11.

## Statistical approach

### Power and sample size justification

As the level of randomization for this SW-CRT is at the practice level, there are several important study design features: *K*, the number of primary care practices, and *m*, the average number of PLWH recruited per practice, as well as the relatedness of individuals within sites (when individual level data are utilized for analysis). Specifically, the *m* participants will be nested (grouped) within the *K* practices. This nesting will lead to additional dependency in outcomes of participants within a practice; the degree of this dependency, the intraclass correlation coefficient (ICC), will contribute to the necessary increase in sample size to maintain the same level of power as would result if the unit of randomization was independent individual participants rather than participants within practices. Prior studies examining the effects of TASSH on BP control have demonstrated improvements in BP control level ranging from 20 to 25% over usual care. We expect a somewhat smaller effect, as we are testing the effect of PF plus TASSH on BP control.

Trials targeting BP control have found ICCs for BP control ranging between 0.02 and 0.06. In addition, preliminary evidence from our UG3 pilot phase suggests that ICC estimates for BP control under UC align with these estimates. Adoption will be measured as outlined above through aggregate data at the site level each month. It is expected that TASSH adoption will be lower than 50% before PF. We expect the estimates in Table 2 to be conservative if the baseline proportion for adoption is less than 40%. We will test our primary and secondary hypotheses at the 5% two-sided type 1 error level. For secondary measures that will utilize individual level data, we expect to enroll 28–32 individuals on average, expecting approximately 10% attrition over the course of the study period, resulting in at least 25 on average per site.

**Table 2 Tab2:** Achieved power for differences in outcomes ranging from 15 to 20%

ICC	At baseline (no PF): 50%		At baseline (no PF): 40%	
	**Difference: 15%** **Odds ratio: 1.9**	**Difference: 20%** **Odds ratio: 2.3**	**Difference: 15%** **Odds ratio: 1.8**	**Difference: 20%** **Odds ratio: 2.2**
**0.01**	**82%**	**97%**	**84%**	**98%**
**0.03**	**79%**	**96%**	**80%**	**96%**
**0.05**	**77%**	**95%**	**78%**	**96%**

Assume 5% two-sided type 1 error, *K* = 30, *m* = 25 (after accounting for 10% attrition, *m* = 28 at time of recruitment)

### Primary outcomes analyses

TASSH adoption will be measured and evaluated as described above, on all adult PLWH who access care through or visit the sites. Aggregate, de-identified data will be collected from sites each month (cross-sectional measures) to assess adoption. To examine the difference in the proportion of individuals indicated as meeting adoption criteria following 12 months of PF compared to adoption during UC, we will utilize a generalized linear mixed model (GLMM). A GLMM regression model will include a fixed effect for time/step interval, a fixed effect for treatment group at time *t*, and random effects for PHC/cluster. We will explore alternatives to these models in sensitivity analyses outlined below.

We will classify four intervals of the PF intervention, each 3 months in duration (start of PF + TASSH to 3 months; 4 to 6 months; 7 to 9 months; 10 to 12 months) to explore the change in adoption over the intervention period. Adoption at the cluster/site level will be described and compared across intervals. To examine whether the rate of adoption increases over time, a GLMM will be used to assess the effect of time on adoption rates. Specifying a main effect of time (categorized as defined above), we will interpret a positive main effect to indicate that rates of adoption increase over time. Covariates strongly related to adoption as well as study design factors which may influence levels of adoption will be identified and may be included in adjusted analyses. Proposed factors include site size and patient characteristics such as sex and age (as a proportion of the total). These will be a limited set of covariates, given the limited degrees of freedom available for these site/cluster-level analyses. Adjustment variables will be identified prior to data exploration and PF initiation. The denominator degrees of freedom for the *F*-test for the intervention effect contrast will be adjusted for the number of clusters and will consider any group level covariates utilized in adjustment [42]. The test of PF intervention to usual care will be evaluated at the two-sided 5% level.

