**Fig. 1 Fig1:**
[figure not shown]
Overview of i-PARiHS and RE-AIM

The pre-implementation phase used the i-PARiHS in inquiring about the existing health system and PHC context to inform the development of a context-specific PF strategy. We assessed barriers and facilitators of integrating TASSH into PHCs for hypertension management through structured facility assessments and in-depth interviews with stakeholders within the PHCs and primary health system in Akwa Ibom. A pilot study was conducted during the pre-implementation phase wherein the feasibility of TASSH plus PF intervention was assessed in two PHCs. The facilities included in the pilot are not participating in the implementation phase.

In the implementation phase, we are using a SW-CRT design to introduce PF at the PHCs. The 30 PHCs were randomly allocated into five cohorts of six PHCs, and all begin in the TASSH only condition, which serves as the usual care control. Figure 2 overviews the stepped wedge design for this study. Given the SW-CRT, the length of time in TASSH alone (without PF) will vary, with a minimum duration of 3 months for the first cohort. Three months prior to the TASSH plus PF experimental condition starting, each cohort will have a training period. During this period, nurses and other staff at the PHCs receive training (or retraining) in delivering TASSH. Once the 3-month training period is completed, the PHCs will participate in a 12-month implementation period during which PF will occur.

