### Study setting and population

Thirty-two PHCs from a network of 59 PHCs across Akwa Ibom were recruited into the study — 2 for the pre-implementation phase and 30 for the implementation phase. These PHCs support a sizeable number of PLWH. Adoption will be measured on all eligible persons to be screened for hypertension. Eligible patients are identified from the roster of PLWH during routine visits and through linkages from community screening and proximal HIV clinics. In the 30 implementation study sites, we will recruit and enroll an average of 28–32 patients, for a maximum of 960 PLWH participants with uncontrolled hypertension to be followed longitudinally for BP outcomes. Eligibility criteria include the following: (1) HIV-positive persons aged 18 years or older; (2) either currently enrolled in HIV treatment services at one of the 30 study PHCs, receiving hypertension treatment services at one of the 30 study PHCs, or can be enrolled at one of the 30 study PHCs to receive hypertension services for the entire study duration; (3) (for those being followed for BP control) have elevated BP between 140–179 mm Hg systolic and/or 90–109 mm Hg diastolic, as determined by the average of the latter two of three separate BP readings during one clinic visit; and (4) be able to provide consent. The inclusion criteria are based on WHO’s CVD treatment guidelines [30–32].

Those who refuse, who are unable to provide informed consent, or with any of the following criteria at baseline will be ineligible for inclusion in the longitudinal BP cohort: (1) BP of ≥ 180/110 mm Hg; (2) known history of kidney disease, heart disease, diabetes mellitus, transient ischemic attacks, stroke, or heart failure; and (3) are pregnant or breastfeeding at the time of enrollment.

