#### Practice facilitators

Senior nurses with extensive clinical and managerial experience working in PHCs as trainers were recruited as practice facilitators to support clinic nurses implementing TASSH. Working with the Akwa Ibom State Directorate of Nursing which oversees the training, planning, and evaluation of capacity building programs, we recruited and hired six senior nurses as practice facilitators. Each practice facilitator will work with six study sites for the study duration. The decision to recruit and hire senior nurses as practice facilitators is due to the hierarchical nursing structure in Nigeria wherein senior nurses are responsible for providing oversight and support of nurses within PHCs. Working within the current nursing structure enhances the sustainability and adoption of TASSH beyond the study period.

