### Secondary outcomes analyses

#### BP control

As noted previously, controlled BP will be defined as systolic blood pressure (SBP) less than 140 mm Hg and diastolic blood pressure (DBP) less than 90 mm Hg. In a closed cohort analysis (i.e., restricted to only enrolled PLWH), we will examine the improvement in BP control on those enrolled during the initial months of the trial. To examine the difference in the proportion of enrolled individuals with BP control during the PF of TASSH to the UC intervals following 12 months of PF, we will use GLMM to assess the intervention effect. A GLMM regression model will include a fixed effect for time interval, a fixed effect for treatment group at time *t*, and random effects for cluster, for individuals within clusters, and for time within cluster. These random effects will accommodate the dependence between outcomes assessed in the same participant over time, as well as for the correlation of individuals within sites. Selected individual-level covariates highly related to BP control will be included for adjustment, including biologic sex. Cluster-level covariates may also be considered for adjustment if possible, such as clinic size. The denominator degrees of freedom for the *F*-test for the intervention effect contrast will take into account any group-level covariates utilized in adjustment.

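### The primary adoption model lists a PHC random effect only, without the time-within-PHC term given to the BP model, so its 5% test can exceed 5%

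*Protocol article*

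**What the plan says.** All places are in the protocol article.

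- **Primary outcomes analyses, data.** "Aggregate, de-identified data will be collected from sites each month (cross-sectional measures) to assess adoption".
- **Primary outcomes analyses, model.** A GLMM with a fixed effect for time or step interval, a fixed effect for treatment group, "and random effects for PHC/cluster. We will explore alternatives to these models in sensitivity analyses outlined below". Denominator degrees of freedom are adjusted for the number of clusters, and "The test of PF intervention to usual care will be evaluated at the two-sided 5% level".
- **BP control.** The GLMM for this secondary outcome has "random effects for cluster, for individuals within clusters, and for time within cluster".
- **Sensitivity analysis.** The GLMM is compared with permutation tests on the active stepped-wedge phase, meaning the periods in which clusters are in different conditions. The section says that GLMMs depend on random-effects assumptions and that the permutation tests do not. No other random-effects structure for adoption is named.
- **Study design.** "The 30 PHCs were randomly allocated into five cohorts of six PHCs".
- **Practice facilitators.** Six facilitators were hired. "Each practice facilitator will work with six study sites for the study duration".

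**The concern.** Adoption measures what a clinic's staff do, counted every month in the same 30 PHCs. With a PHC effect alone, two patients at one PHC are as strongly correlated when seen many months apart as when seen in the same month. In a binomial model, all remaining scatter is then treated as sampling error. If a PHC's adoption level also moves between periods for its own reasons, that movement is real variance with no place in the model.

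The PF effect in a stepped wedge is estimated largely from change within PHCs over time, so this is the variance that governs its standard error. The authors allow for such movement in BP control but not in the outcome that carries the primary 5% test. At stake is whether the primary confidence interval is wide enough and whether a significant PF effect can be taken at its stated error rate.

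**Working it through.** **1. The plan's own power figures.** Table 2 uses K = 30, m = 25, two-sided 5% and ICC 0.01, 0.03 and 0.05. The standard stepped-wedge variance with fixed period effects and a cluster intercept only reproduces it, taking 6 periods, five cohorts of six, and 25/6 patients per PHC-period. For 50% plus 15 points at ICC 0.05:

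- Cell variance σ² = 0.25 × 0.95 / (25/6) = 0.057; cluster variance τ² = 0.25 × 0.05 = 0.0125.
- Design sums: I = 30, T = 6, U = 90, W = 1980, V = 330.
- Variance = Iσ²(σ² + Tτ²) / [(IU − W)σ² + (U² + ITU − TW − IV)τ²] = 0.22572 / (720 × 0.057 + 2520 × 0.0125) = 0.22572 / 72.54 = 0.00311, so SE = 0.0558.
- Power = Φ(0.15/0.0558 − 1.96) = 76.7%, against 77% in Table 2.

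All 12 cells agree within 0.5 point, so the sample-size stage also fits a model without PHC-by-time variance. Lowering the correlation ratio to 0.5 moves Table 2 by less than 1 point, because it has only about 4 patients per PHC-period.

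**2. Type I error of the primary test.** Let r be the ratio of between-period to within-period correlation in a PHC, and n the patients per PHC-quarter. The article gives neither, nor an ICC for adoption. Figure 2 is not shown, so 3-month steps are assumed.

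The model takes the residual variance of a PHC-quarter proportion as σ²(1 − ICC)/n, where σ² is now the total variance of the binary outcome. The true value adds σ² × ICC × (1 − r). Since the PF effect is estimated mostly within PHCs, approximately:

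- true SE / model SE = √[1 + n × ICC × (1 − r)/(1 − ICC)]
- type I error = 2[1 − Φ(1.96 / that ratio)]

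| ICC | n | r | SE ratio | Type I, by hand | Type I, full sandwich calculation |
|---|---|---|---|---|---|
| any | any | 1 | 1.00 | 5% | 5% |
| 0.03 | 60 | 0.9 | √1.186 = 1.09 | 7.2% | 7.0% |
| 0.03 | 60 | 0.8 | √1.371 = 1.17 | 9.4% | 9.0% |
| 0.05 | 60 | 0.9 | √1.316 = 1.15 | 8.8% | 8.6% |
| 0.05 | 60 | 0.8 | √1.632 = 1.28 | 12.5% | 12.2% |
| 0.05 | 100 | 0.9 | √1.526 = 1.24 | 11.3% | 11% |
| 0.05 | 100 | 0.8 | √2.053 = 1.43 | 17.1% | 17% |
| 0.01 | 15 | 0.8 | √1.030 = 1.02 | 5.3% | within 5.1–5.6% |

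The last column uses the whole design: generalized least squares with a PHC-intercept working covariance, and its model variance set against the sandwich variance under the true covariance.

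**3. Simulation of the binomial-logit GLMM under no PF effect.** ICC 0.05, 20 patients per PHC-month (60 per quarter):

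| r | Runs | PHC effect only: normal / 28-df t | With PHC-by-step effect: normal / 28-df t | SE ratio before / after |
|---|---|---|---|---|
| 1.0 | 2000 | 5.1% / 3.8% | not run | 1.00 |
| 0.8 | 1000 | 10.5% / 9.0% | 5.0% / 4.4% | 1.22 / 0.99 |
| 0.5 | 600 | 18.0% / 16.8% | 4.7% / 3.7% | 1.49 / 0.99 |

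The 28-df reference lowers the rejection rate a little but leaves the standard error too small. The added term brings the test back to about 5%.

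A separate 600-run set at ICC 0.03 gave only 4.5% (r = 0.9) and 5.5% (r = 0.8). That set ran low throughout: it gave 3.2% at r = 1, where 5% is expected. A larger repeat of the two ICC 0.03 settings lay close to the analytic values.

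**4. Facilitators.** 6 facilitators × 6 sites = 36 assignments. The article counts "2 for the pre-implementation phase and 30 for the implementation phase".

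**The case against.** **The article is condensed.** It does not say that the PHC effect is the only one, and it uses the plural. The covariance structure could be completed in an analysis plan that is not shown. This stands as a caution. But the next section names time within cluster as a separate term, so the text as written gives the primary outcome the weaker structure.

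**The model may not be binomial.** Monthly aggregates, site-level analyses and an F-test would also fit a Gaussian model on clinic-month proportions, whose residual absorbs part of the missing variance. Simulated type I error (normal reference, ICC 0.05, 20 per month) is then 8.1% at r = 0.8 and 12.0% at r = 0.5 for step-level variation, and 4.8% for purely month-level variation at r = 0.8. So this reading is less affected but not immune. The odds ratios in Table 2 point towards a logit model.

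**The plan has a safeguard.** The permutation test does not need the correlation assumptions, and its restriction to the active phase has a stated reason. This mitigates the problem, but the test has no stated role if it disagrees with the primary result.

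**Stronger readings that the article does not support.**

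- A reader might infer that the 5% level is certainly breached, or breached several-fold. At r = 1 it is not breached, and with small cells and low ICC the excess is trivial. A figure as high as 27% needs ICC 0.10 (with r = 0.8 and 100 per quarter), above the 0.01 to 0.05 of Table 2 and the 0.02 to 0.06 cited for BP control.
- Nurse turnover and drug stock-outs are plausible sources of drift but are not described.
- Six times six against 30 might be read as an error, or as grounds for a facilitator random effect. Sharing of sites is not excluded, and a term with six levels would be a matter of preference.

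**Conclusion.** The point holds conditionally. As written, the primary GLMM omits a variance component that the plan includes for BP control. Whenever PHC-by-time variance in adoption is above zero, a binomial or logit model of this form gives too small a standard error and a test above 5%.

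Under the assumptions in the table (ICC 0.03 to 0.05, ratio 0.8 to 0.9, 60 to 100 patients per PHC-quarter), type I error is about 7% to 17%. With 15 patients per cell and ICC 0.01 it is about 5% to 6%. The direction is secure; the size is not, because the correlation ratio, the cell size and the adoption ICC are all assumed. The point does not undermine Table 2. The facilitator count is a separate matter of consistency and has no bearing on these figures.

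**What to change.** - Add a random PHC-by-interval effect to the primary adoption GLMM, matching the time-within-cluster term in the BP control model, and keep the cluster-based denominator degrees of freedom.
- Report the planned permutation p-value beside the primary result.
- Make the change before outcome data are examined by treatment condition.

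The cost is one more variance parameter and somewhat wider intervals. No new data are needed. If the added variance is estimated near zero, the analysis is practically the one now planned.

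Separately, reconcile the Practice facilitators section (six facilitators, six sites each) with the 30 PHCs, for example by stating whether any sites are shared.

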### Secondary outcomes analyses

#### BP control

As noted previously, controlled BP will be defined as systolic blood pressure (SBP) less than 140 mm Hg and diastolic blood pressure (DBP) less than 90 mm Hg. In a closed cohort analysis (i.e., restricted to only enrolled PLWH), we will examine the improvement in BP control on those enrolled during the initial months of the trial. To examine the difference in the proportion of enrolled individuals with BP control during the PF of TASSH to the UC intervals following 12 months of PF, we will use GLMM to assess the intervention effect. A GLMM regression model will include a fixed effect for time interval, a fixed effect for treatment group at time *t*, and random effects for cluster, for individuals within clusters, and for time within cluster. These random effects will accommodate the dependence between outcomes assessed in the same participant over time, as well as for the correlation of individuals within sites. Selected individual-level covariates highly related to BP control will be included for adjustment, including biologic sex. Cluster-level covariates may also be considered for adjustment if possible, such as clinic size. The denominator degrees of freedom for the *F*-test for the intervention effect contrast will take into account any group-level covariates utilized in adjustment.

#### Implementation fidelity

We will assess implementation fidelity of TASSH as a potential mechanism that may explain the effect of PF on our primary outcome of BP control. Analyses will begin with descriptive analyses of levels of TASSH implementation fidelity. Using validated surveys, we will also assess practice-level, provider-level, and patient-level moderators that may influence implementation fidelity of TASSH within the PHCs. Finally, we will examine the association between the proportion of BP control at 12 months following PF initiation and levels of implementation fidelity for TASSH. Quantitative analysis of implementation fidelity will consist of descriptive statistics to provide documentation and description of fidelity to each of the components of TASSH. Associations between BP control and implementation fidelity will be evaluated using both the methods outlined by Vanderweele [43, 44], along with structural equation modeling (SEM) methods. We will estimate a path model to investigate relationships between BP control and implementation fidelity. Implementation fidelity will be identified as individual and simultaneous predictors of BP control at the site level. Practice-level, provider-level, and patient-level variables, which may influence implementation fidelity, will be considered in the model. In addition to the direct effects of each variable, the indirect effects from each variable to BP control via mediator variables will be estimated. This analysis will examine potential pathways in which BP control is influenced by fidelity to TASSH and characteristics of practices, providers, and PLWH in the trial [45]. Fit indices will be evaluated for all path models to ensure adequate model fit.

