**Design:**

In partnership with the Nigerian Federal Ministry of Health (FMOH) and community organizations, the MAP-IT trial takes place in 30 PHCs. The i-PARiHS framework guided pre-implementation needs assessment. The RE-AIM framework will guide post-implementation activities to evaluate the effect of practice facilitation on the adoption, implementation fidelity, and sustainability of a hypertension program, as well as blood pressure (BP) control. Using a SW-CRT design, PHCs sequentially crossover from the hypertension program only (usual care) to hypertension plus practice facilitation (experimental condition). PHCs will recruit and enroll an average of 28–32 patients to reach a maximum of 960 PLWH participants with uncontrolled hypertension who will be followed longitudinally for BP outcomes.

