**Fig. 2 Fig2:**
[figure not shown]
Stepped wedge study design

Nurses at these PHCs will implement all aspects of TASSH in their clinical care for PLWH with uncontrolled hypertension. PFs will support nurses during the 12-month period by helping with hypertension treatment issues and addressing barriers to TASSH implementation. The RE-AIM framework defines measures to evaluate the effect of PF on TASSH adoption after 12 months of PF compared to TASSH adoption without PF (primary outcome). RE-AIM facilitates evaluation of the effect of PF on BP control (secondary outcome) and the level of TASSH implementation fidelity (secondary outcome).

Following each cohort’s 12-month implementation phase, each PHC transitions to the post-implementation phase (follow-up period). Nurses will continue to implement TASSH. However, PF will end. Six months into this post-implementation period (18 months following the start of PF), we will evaluate the sustainability of TASSH within the PHCs (secondary outcome). Figure 3 provides an overview of the study design including the pre-implementation, implementation, and post-implementation phases.

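### The trial sets out to evaluate the effect of PF on implementation fidelity, but no stated analysis compares fidelity between PF and usual care

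*Protocol article*

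**What the plan says.** **Objective.** The abstract (Design) says RE-AIM will guide activities to "evaluate the effect of practice facilitation on the adoption, implementation fidelity, and sustainability of a hypertension program". The Study design section, in the text after Figure 2, adds: "RE-AIM facilitates evaluation of the effect of PF on BP control (secondary outcome) and the level of TASSH implementation fidelity (secondary outcome").

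**Status and timing.** Under Secondary outcomes: "Secondary outcomes include BP control, implementation fidelity, and TASSH sustainability", and "Fidelity to TASSH will be measured throughout the study and defined by five dimensions".

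**Control condition.** Study design says of the 30 PHCs that "all begin in the TASSH only condition, which serves as the usual care control".

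**Testing.** Power and sample size justification: "We will test our primary and secondary hypotheses at the 5% two-sided type 1 error level".

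**Analysis.** The Implementation fidelity subsection of Secondary outcomes analyses states: "Quantitative analysis of implementation fidelity will consist of descriptive statistics to provide documentation and description of fidelity to each of the components of TASSH". It also plans to look at practice-, provider- and patient-level moderators of fidelity, and to examine "the association between the proportion of BP control at 12 months following PF initiation and levels of implementation fidelity for TASSH". It names VanderWeele's methods and structural equation modelling for this. In the path model fidelity is a site-level predictor of BP control, and practice, provider and patient variables are the ones named as possible influences on fidelity.

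**The concern.** The objective asks whether PF changes fidelity. The analysis section describes fidelity and relates it to BP control. These are different questions, and a SAP that followed the analysis section faithfully would not answer the first.

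The design could answer it. Every PHC contributes time under usual care and time under PF, in randomised order, and fidelity is said to be measured across the whole study. Adoption and BP control are each given a GLMM with a time effect and a treatment effect; fidelity is not. Without such a model, the only PF-versus-usual-care reading open to a later author is an unadjusted one. The article's own Limitations section names confounding by temporal trends as a notable weakness of the design and relies on adjustment in modelling to deal with it.

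**Working it through.** The article gives no sample size, power or effect figure for fidelity, so there is nothing to reproduce. The check is mainly textual.

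**1. Does any stated analysis contain a PF-versus-usual-care term for the outcome?**

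| Outcome | Stated analysis | PF vs usual care, adjusted for time? |
|---|---|---|
| Adoption (Primary outcomes analyses) | GLMM: time/step, treatment group, PHC random effect | Yes |
| BP control | GLMM: time interval, treatment group, random effects for cluster, individual and time within cluster | Yes |
| Fidelity, descriptive part | Descriptive statistics by TASSH component | No |
| Fidelity, moderators | Practice, provider and patient factors acting on fidelity | No; PF is not named |
| Fidelity, association and path models | BP control as outcome, fidelity as predictor | No; fidelity is not regressed on PF |

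**2. Could the association data set yield the effect anyway?** It is set 12 months after PF initiation. By then all 30 PHCs have received PF, so a PF indicator equals 1 at every site. A constant cannot be given a coefficient. Estimating the effect needs fidelity data from usual-care periods and a time-adjusted PF term, and the subsection states neither.

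**3. Would the missing model be feasible?** This is an illustration only. Figure 2 is not available, and the article fixes neither a fidelity scale nor a measurement frequency. Assumptions: quarterly steps; cohort c (1 to 5) starts PF in quarter c, with the baseline as quarter 0; four PF quarters each; six PHCs per cohort; one score per PHC-quarter with total SD 1; correlation ρ between quarters of the same PHC; quarters after PF ends excluded. The model has fixed quarter effects, a PF term and a PHC random intercept, fitted by generalised least squares. Detectable effect at 80% power = (t₀.₉₇₅ + t₀.₈₀ on 28 df) × SE = (2.048 + 0.855) × SE = 2.903 × SE.

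| Treatment of the 3-month training period | ρ = 0.3 | ρ = 0.5 | ρ = 0.7 |
|---|---|---|---|
| Counted as usual care: SE | 0.206 | 0.183 | 0.146 |
| Counted as usual care: detectable effect | 0.60 | 0.53 | 0.42 |
| Last pre-PF quarter is training, excluded: detectable effect | 0.77 | 0.70 | 0.56 |
| Separate training quarter added before PF, excluded: detectable effect | 0.74 | 0.66 | 0.52 |

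The model is estimable under all three layouts, with a range of about 0.4 to 0.8 SD.

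**4. What would an unadjusted comparison risk?** Under the first layout there are 1 + 2 + 3 + 4 + 5 = 15 usual-care cohort-quarters, whose quarter numbers sum to 20, so their mean is 20/15 = 1.33. There are 5 × 4 = 20 PF cohort-quarters, whose quarter numbers sum to 90, so their mean is 90/20 = 4.50. The gap is 3.17 quarters. If fidelity rose by 2 points per quarter for reasons unrelated to PF (an assumed trend on an unspecified scale), a raw comparison would show 3.17 × 2 = 6.3 points with no PF effect at all.

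**The case against.** **The mechanism framing implies a PF-to-fidelity path.** The fidelity subsection introduces fidelity as something that may explain how PF acts on BP control, and it plans indirect effects through mediators. A full mediation analysis would include a model of fidelity on PF. This stands as a reason not to say the effect will never be estimated. It does not supply the analysis: the methods are applied to the relation between BP control and fidelity, PF is not named as the exposure, and the stated time point has no variation in PF.

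**The promise is loosely worded.** The Study design sentence can be read as concerning only the level of fidelity. The abstract also lists sustainability under effect, although the Sustainability subsection plans only descriptive summaries and a time effect. No fidelity hypothesis is written out, so the general statement on 5% testing adds little. All fair, but the abstract's wording on fidelity is explicit, and the two places still need to agree.

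**Part of the ground is already covered.** Table 1 defines adoption as the proportion receiving all applicable protocol components, and adoption has a time-adjusted GLMM. That overlaps with the adherence dimension of fidelity. Quality, participant responsiveness and programme differentiation are not covered in this way. A reader might infer that the randomised comparison is thrown away for fidelity altogether; that goes too far.

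**The bias belongs to an analysis nobody has planned.** Correct. The article proposes no raw PF-versus-usual-care comparison of fidelity. The 6.3 points illustrate what such a comparison could do under an assumed trend and schedule.

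**Comparable usual-care data are not assured.** Fidelity is to be assessed partly from the facilitator's perspective, and that source may not exist before PF begins. Staff are trained or retrained in TASSH during the three months before PF, which could itself move fidelity. Both points stand and shape the fix.

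**This could be left to the SAP.** Silence could be. Here the article positively states what the fidelity analysis consists of, and that statement does not match the objective.

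**Conclusion.** The mismatch is real and should be resolved. The article undertakes to evaluate the effect of PF on implementation fidelity, and the fidelity analysis it sets out contains no estimate of that effect. This affects a secondary outcome; the primary analysis of adoption is not touched.

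The conclusion rests on the text and on no numerical assumption. The figures for detectable effects (about 0.4 to 0.8 SD) and for the 3.17-quarter gap depend on the assumed quarterly schedule and the assumed correlations, and serve only to show that the missing model is feasible with modest precision.

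The documents do not support concluding that the trial cannot estimate the effect, or that a biased estimate is planned. The supported statement is narrower: no analysis estimating PF versus usual care on fidelity is stated.

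**What to change.** In the Implementation fidelity subsection, add a stepped-wedge mixed model with fidelity as the outcome:

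- fixed effects for time interval and PF status, and a PHC random effect;
- a time-within-PHC random effect only if each PHC-period has several fidelity measurements, since with one score per period it cannot be separated from residual error;
- denominator degrees of freedom based on the 30 PHCs;
- only fidelity measures collected in the same way under usual care and PF;
- the 3-month training period treated separately from usual care;
- the result reported as an estimate with a confidence interval.

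If fidelity cannot be measured comparably in usual care, reword the abstract and the Study design sentence so that the aim is to describe fidelity and explore it as a mechanism.

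The cost is one more model of modest precision, or a change of wording. No new data collection is needed if at least some fidelity tools are already used in the same form in both conditions; the sponsor should confirm this, because the article does not show it.
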